### Communication

In addition to the scheduled follow-up calls, participants are encouraged to call the study telephone number with any questions they may have. The cancer advisory unit at the patient advocate organization, the Norwegian Cancer Society [73], and the Breast Cancer Oncology Group (Norwegian Breast Cancer Group) [74] also have basic information about the CABC trial, in case the participants call them for support. Furthermore, the CRN and the Norwegian Breast Cancer Society share information about the trial occasionally through their social media platforms and newsletters. These channels will also be used to inform people about published results. In addition to scientific publications and presentations of results at scientific conferences, results will be communicated to the public through various media outlets after the study end. Any changes to the protocol will be recorded simultaneously at the ClinicalTrials.gov registry [75].

### Outcome Measures

#### Surveys

Outcomes are assessed with 2 digital surveys: the ongoing CRN PROMs survey and the study-specific CABC survey (Table 1).

**Table 1 table1:** Detailed information on outcome measures that will be obtained from the CABC^a^ survey and the CRN PROMs^b^ survey.

Outcome(s)				Assessed with		Number of items, n
**CABC survey: ≥7, 13, 24, and 35 months after diagnosis**						
	**Primary outcome (from 7 to 13 months after diagnosis)**					
		Perceived stress	Cohen 10-item Perceived Stress Scale [76]		10	
	**Secondary outcomes (all time points)**					
		Perceived stress	Cohen 10-item Perceived Stress Scale [76]		10	
		Health and health-related quality of life	RAND Corporation 36-Item Short Form Health Survey [11]		36	
		Coping	Theoretically Originated Measure of the Cognitive Activation Theory of Stress [77]		7	
		Fatigue^c^	Chalder’s Fatigue Scale [78]		11+2^d^	
		Awareness/mindfulness	Baer’s Mindfulness Questionnaire [49,79]		15	
		Distress	Patient Health Questionnaire [80]		4	
		Sleep	The Survey of Shift Work, Sleep and Health [81]		10	
		Work and use of social services^e^	Work, use of social services, and Ability Index [82] and single-item question [83]		3	
**CRN PROMs survey: ≥21 days and 14 and 36 months after diagnosis**						
	**Secondary outcomes (all time points)**					
		Cancer-related quality of life	European Organization of Research and Treatment of Cancer-Core Quality of Life Questionnaire [84]		30	
		Breast cancer–related quality of life	European Organization of Research and Treatment of Cancer-Core Quality of Life Questionnaire: Breast Cancer–Specific Module [85]		23	
		Neuropathy/neuropathic pain, vaginal symptoms, arthralgia	Functional Assessment of Cancer Therapy: Gynecologic Oncology Group—Neurotoxicity and Endocrine Symptoms [86]		8	
		Fatigue	Chalder’s Fatigue Scale [78]		11+2^d^	
		Workability and use of social services	Work Ability Index [82] and single-item question [83]		3	
		Stress^f^	Stress Experience Scale [87]		1	
		Background questions	Educational level, living with children <18 years (yes/no), household income, living situation, income, physical activity level (light and high intensity), smoking and alcohol habits, and height and weight		11	

^a^CABC: Coping After Breast Cancer.

^b^CRN PROMs survey: Cancer Registry of Norway patient-reported outcome measures survey.

^c^Chalder’s Fatigue Scale is only included at baseline and at month 24 by the CABC survey because it is assessed with the CRN PROMs survey at 13 and 36 months after diagnosis.

^d^The survey sent to participants diagnosed in 2020 included the 11-item Chalder’s Fatigue Scale, whereas questions on duration and extent of fatigue symptoms [88,89] were added to the survey sent to participants enrolled and followed up after 2021.

^e^Only included at 24 months of follow-up in the CABC survey.

^f^Stress assessed as 1 item is not defined as a secondary outcome but can be used in exploratory analysis.

#### The CRN PROMs Survey

The CRN PROMs survey is sent to all patients with breast cancer 21 days and 14 and 36 months following diagnosis. Several measures from the CRN PROMs survey are included as secondary outcomes in this study as outlined in Table 1.

Fatigue is assessed using variants of Chalder’s Fatigue Scale rating subjective physical and mental features of fatigue [78,88,89]. Peripheral neuropathy, vaginal symptoms, and arthralgia are measured by the Functional Assessment of Cancer Therapy/Gynecologic Oncology Group—Neurotoxicity and Endocrine Symptoms questionnaire [86] (only available for patients diagnosed from 2021). Quality of life is assessed by the 30-item European Organization of Research and Treatment of Cancer-Core Quality of Life Questionnaire (EORTC QLQ-C30) [84] and its Breast Cancer–Specific Module (EORTC QLQ-BR23) [85]. Report on work-related outcomes including use of social services is assessed with the Work Ability Index [82] and single-item question [83].

The CRN PROMs survey also contains self-reported information on background data including educational level, living situation, number of children less than 18 years, income, physical activity level, smoking and alcohol habits, height, and weight (Table 1).

#### Coping After Breast Cancer Questionnaire

Participants receive the baseline CABC survey at approximately 7 months after diagnosis and the follow-up CABC surveys 13, 24, and 35 months after diagnosis (Figure 1). The follow-up surveys were sent about 1 month after the CRN PROMs surveys, in order for participants not to confuse the 2 data collections.

The Cohen 10-item Perceived Stress Scale [76] in the CABC survey will be used to assess the primary outcome: 6-month change in perceived stress (from 7 to 13 months following diagnosis) between each of the intervention groups and TAU (Table 1).

The following secondary outcomes are also obtained from the CABC survey: distress ranging from sadness and worry to anxiety and depression, as measured by the Brief Version of the Patient Health Questionnaire for Depression and Anxiety [80]. (Health-related) quality of life is measured by the RAND Corporation 36-Item Short Form Health Survey (RAND-36). RAND-36 assesses 8 health concepts: physical functioning, role limitations caused by physical health problems, role limitations caused by emotional problems, social functioning, emotional well-being, energy/fatigue, pain, and general health perceptions [11]. Mindfulness is assessed using the 15 items from Baer’s 5 Facet Mindfulness Questionnaire [49]. Sleep (duration and quality) is measured by items from the Norwegian Shift Work, Sleep and Health survey [81]. Coping, defined as 3 dimensions of response outcome expectancies related to an individual’s ability to handle stressors and challenges in everyday life related to coping, hopelessness, and helplessness, is measured by the Theoretically Originated Measure of the Cognitive Activation Theory of Stress [77].

As there is no CRN PROMs survey 24 months after diagnosis, the work-related outcomes are included in the CABC survey after 24 months, whereas Chalder’s Fatigue Scale is included at baseline and at month 24 (Table 1).

#### Other Outcomes

The study will further explore characteristics of those who respond to the CABC trial (responders versus nonresponders) and those who complete the interventions (at least 7 out of 10 modules of StressProffen-CBI or StressProffen-MBI) and their counterparts. Data from the CRN PROMs survey 21 days prior to diagnosis will be used to assess differences in CABC trial invitation responders and nonresponders. Differences in intervention effects (primary and secondary outcomes) between StressProffen-CBI and StressProffen-MBI will also be explored.

Participant data will be linked to the Norwegian Labor and Welfare Administration database, Statistics Norway, the CRN, the Norwegian Patient Registry, the Norwegian Prescription database, and the Norwegian Cause of Death Registry. In addition to data from the surveys, data from the registries will be used for exploratory analysis, including predictors of intervention effects and long-term effects of study participation on comorbidities, relapse and new cancers, and mortality. Detailed and objective information on work participation including sick leave, disability pension, and use of social services will also be obtained. These linkages will enable long-term follow-up of participants in the CABC trial until study end (currently 2035).

### Monitoring Compliance

Those who have not completed the CRN PROMs survey and the CABC survey automatically receive 1-2 reminders (unless they have opted out of receiving reminders) during a 30-day period. To ensure as high participation rate as possible, the CABC survey sent 13 months after diagnosis is available for 45 days and includes 2 additional reminders: 1 by phone and 1 by a standard motivational letter. There is no manual review or monitoring of survey responses during the trial. Survey data and participant data (ie, name, phone number, randomization string, scheduled and actual phone calls, and participant dropouts) are stored in CRN databases protected with 2-factor authentication. Access to survey data is limited to selected employees from the CRN, while participant data are further restricted to employees involved in the CABC study.

In addition to using survey data for monitoring compliance, system usage data (eg, the number of modules completed and time spent on each module and between modules) are logged and stored at the Services for Sensitive Data at the University of Oslo. Only approved study personnel have access to this information prior to study end.

### Pilot Study

Before study implementation in 2021, a pilot study with 23 women (of 59 invited) was conducted to inform the need for adjustments prior to the RCT. Adjustments included minor rewordings of the informed consent, scheduling additional follow-up calls, and reducing the number of items in the CABC survey (eg, the 24-item version of Baer’s Mindfulness Questionnaire [90] was replaced with the 15-item version [49,79]).

### Ethical Considerations

Data collection in the CRN PROMs survey is based on informed consent—Article 6 (1) (a) and Article 9 (2) (a) of the European Union’s General Data Protection Regulation. The Regulations on Population-Based Health Surveys give additional conditions for data collection and processing and what data can be accessed in this study.

All participants are asked to provide informed consent by responding to the CABC survey. Participants are informed that consent also implies consent to have their data linked to several national registries. This includes the CRN; the Norwegian Breast Cancer Registry, where cancer subtypes are recorded; the Norwegian Patient Registry; the Norwegian Cause of Death Registry; and the Norwegian Prescription Database (for comorbidity, morbidity, mortality, and prescription data). Data are also linked with the Norwegian Labor and Welfare Administration Database and Statistics Norway to obtain information on work participation including sick leave and disability. Registry linkages can currently be performed until the end of the study (ie, up to December 31, 2035).

As the intervention is digital, including digitally completed outcome measures, no methods to identify adverse effects have been identified. Further, there is no monitoring committee and hence no stopping guidelines have been implemented. Participants can withdraw from the study at any time and without stating their reasons for doing so. This will not have any consequences for their further treatment. Participants are also free to stop using the app whenever they wish to do so.

The study is approved by Regional Committee for Medical Research Ethics Southeast Norway (reference number 32637 “Stressmestring etter brystkreft” [CABC] and registered at ClinicalTrials.gov, NCT04480203 [CABC]).

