### Potential Intervention Harms

The CBI and MBI interventions have no known harms. A feeling of disappointment might arise if the participant does not feel that their stress level has been reduced during the study period. Although the vast majority of literature says otherwise, it cannot be completely ruled out that meditation-based therapies may lead to distress [72].

As the participants do not have access to individual therapy through the study, participants in both intervention groups are encouraged to seek professional help from their primary caregiver, should they wish/feel a need to do so.

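### The reason given for having no adverse-effect method does not fit a plan that names distress as a possible harm and measures it in all three arms, and no count of participants who worsen is set out.

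*Protocol article*

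**What the plan says.** Ethical Considerations gives a reason as well as a position: because both the intervention and the outcome questionnaires are digital, "no methods to identify adverse effects have been identified". It continues that "there is no monitoring committee and hence no stopping guidelines have been implemented".

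Potential Intervention Harms opens with "The CBI and MBI interventions have no known harms" but then qualifies this: "it cannot be completely ruled out that meditation-based therapies may lead to distress".

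Under Coping After Breast Cancer Questionnaire, a secondary outcome is "distress ranging from sadness and worry to anxiety and depression, as measured by the Brief Version of the Patient Health Questionnaire for Depression and Anxiety". Table 1 lists this 4-item score and PSS-10 in the trial's own survey, at baseline (about 7 months after diagnosis) and at 13, 24 and 35 months. The Randomization section shows that controls also receive the follow-up surveys.

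Monitoring Compliance adds: "There is no manual review or monitoring of survey responses during the trial". Specific Hypotheses frames distress and perceived stress only as reductions. Statistical Analysis compares outcomes between groups by intention to treat and per protocol, with two-tailed tests, and says that a fuller description of the analysis will follow.

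**The concern.** The article names one plausible harm, and the trial measures that harm before and after access to the app with a randomised comparator. Digital completion of the questionnaires is how this is done; it is not a reason why it cannot be done.

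This is more than a detail left to the analysis plan. It is a positive statement with a reason attached, and an analysis plan written to agree with it would contain no harms analysis. The distress data would then be read only as evidence of benefit, mainly through means, and a mean can improve while some participants get worse. The Discussion and Conclusions look ahead to use in clinical practice, where benefit has to be weighed against harm.

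**Working it through.** **Sections side by side**

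| Question | What the article provides |
|---|---|
| Is a harm named? | Yes: distress (Potential Intervention Harms) |
| Is it measured? | Yes: 4-item distress score and PSS-10 (Table 1) |
| In all arms, before and after access? | Yes: baseline, then 13, 24 and 35 months |
| Is it described as a harm measure? | No |
| Is individual worsening defined or counted? | No |
| Are adverse events recorded? | No provision is described |
| Are responses reviewed during the trial? | No (Monitoring Compliance) |

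**Number analysed per arm.** Sample Size Calculations gives a difference of 3, SD 6, a significance level of 2.5% and 80% power. The normal approximation is n = 2(2.241 + 0.842)²/(3/6)² = 76.0, so 77 per arm and 231 for three arms. The exact t test gives 77.3, so 78 per arm and 234 in total. Both agree closely with the stated 235 (235/3 = 78.3). The enlarged target in Results is 430; at the assumed 70% completion, 430 × 0.70/3 = 100 per arm. Results also says that completion was running below expectation. With 430 enrolled, 78 per arm corresponds to 234/430 = 54% completion. I use 78 and 100 as the range.

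**What the planned comparison of means can show.** For a 0.5 SD average worsening at two-sided 2.5%:
- 78 per arm: 0.5 × √(78/2) = 3.12; 3.12 − 2.24 = 0.88; power about 81%.
- 100 per arm: 0.5 × √(100/2) = 3.54; 3.54 − 2.24 = 1.29; power about 90%.

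The 95% half-width, 1.96 × √(2/n), is 0.31 SD and 0.28 SD respectively.

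**What a mean can hide.** Illustration with assumed figures: relative to control, 90% of an app arm improve by 4 PSS-10 points and 10% worsen by 6. The mean effect is 0.9 × (−4) + 0.1 × 6 = −3.0, exactly the design effect, with one participant in ten worse off.

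**What a worsening table could show.** The half-width of the difference between two arms is 1.96 × √(2p(1 − p)/n). The article gives no rate of worsening, so p is an assumption, taken as equal in both arms.

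| Assumed p | 78 per arm | 100 per arm |
|---|---|---|
| 5% | 6.8 points | 6.0 points |
| 10% | 9.4 points | 8.3 points |
| 20% | 12.6 points | 11.1 points |

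If 5% or 10% of controls worsen, 80% power at two-sided 5% needs about 20% or 27% in an app arm with 78 per arm, and about 17.5% or 25% with 100.

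**The case against.** The strongest reply is that the sentence stands beside those on the monitoring committee and stopping guidelines, and so concerns detection while the trial runs. A 4-item score first repeated about six months after baseline is an outcome measure, not a way of catching adverse events as they occur. That reading is fair, and the proposal here claims only an end-of-trial assessment. It does not rescue the stated reason: digital outcomes do not prevent a harm assessment.

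A reader might infer that the article says adverse effects cannot be identified, or that the trial would have nothing to say about harm because it never looked. The documents support neither. The article says only that no methods had been identified. Distress, perceived stress and quality of life are compared with two-tailed tests, so an average worsening could be seen. The Other Outcomes section adds exploratory registry follow-up of comorbidity, relapse or new cancers, and mortality. The remark on no known harms describes prior knowledge and is qualified in the same section; it is not a planned conclusion.

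It can also be said that a threshold and a table belong in the analysis plan, and that the stored scores allow any rate to be calculated later. Both points are true and reduce the weight of the concern. What remains is that the published statement points the analysis plan away from such a table, and that a threshold chosen after seeing the data would carry less weight.

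Finally, the table would be imprecise for the minority it is meant to reveal. That stands. Nor should a zero-event bound (3/78 = 3.8%) be used to promise more, because some scores will worsen in every arm, including controls.

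**Conclusion.** The concern holds in limited form. The rationale in Ethical Considerations is inconsistent with Potential Intervention Harms and with the outcome schedule. As written, harm would appear only as mean differences in outcomes framed as benefits, or in exploratory registry data. A group-average worsening of about 0.5 SD would probably be found (81 to 90% power); deterioration in a minority could be masked.

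A worsening table would estimate the between-arm difference to within about 8 to 9 percentage points at a 10% rate. This assumes 78 to 100 analysed per arm and equal rates of worsening; across rates of 5 to 20% the half-width runs from 6.0 to 12.6 points. That is enough to show a large excess, but it cannot exclude rare harm. The change is worth making because the data already exist; the point does not undermine the design.

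**What to change.** Revise the sentence in Ethical Considerations so that it agrees with Potential Intervention Harms and the questionnaire section. State that no adverse-event detection takes place during the trial, if that is the intention, and that the distress and PSS-10 scores will also serve as an end-of-trial harm measure.

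Before outcome data are analysed, pre-specify one descriptive table. For each arm, give the number and percentage whose distress or PSS-10 score worsens from baseline to 13 months by a pre-stated amount, and for each app versus treatment as usual give the difference with its 95% confidence interval. State that the precision is modest.

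The cost is one table from data already collected, with no added burden on participants. The sponsor must choose and justify a worsening threshold in advance.

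Distress mentioned in the support calls should be left out unless call content was recorded. Monitoring Compliance lists the scheduled and actual calls among the stored data but not what was said, and Follow-up describes these calls only for the intervention groups, so there would be no comparator.

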### Sample Size Calculations

Power calculation in the CABC trial was conducted on the primary outcome (ie, 6-month between-group difference in perceived stress) using independent sample *t* tests. The α level was adjusted for multiple comparisons (comparing 2 intervention groups with 1 control group for each outcome) by setting the significance level to 2.5%. Estimates of effect sizes and SDs were retrieved from previous StressProffen interventions on multiple groups of patients with cancer, which found a mean difference in perceived stress of 2.8 and SDs of 6.6 and 8.3 in the case and control groups, respectively [70]. As the CABC trial includes a more homogenous population (only female patients with breast cancer), the effect size was set to 3 and the SD to 6.

With an estimated 80% power to detect a difference between 1 of the intervention groups and the control group, a sample size of 235 participants is needed. With an assumed completion rate of 70%, a total of 335 participants will need to be enrolled, 70 in each group.

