### Specific Hypotheses

The CBI and MBI groups will achieve a statistically significant larger reduction in perceived stress after 6 months of access to the interventions (13 months after diagnosis) compared with the TAU control group (*primary outcome*).The CBI and MBI groups will achieve a significantly larger reduction in perceived stress, distress, fatigue, peripheral neuropathy, vaginal symptoms, and arthralgia and a significantly larger improvement in quality of life, mindfulness, sleep, coping, and work-related outcomes 13, 24, 35, and 36 months after diagnosis compared with the TAU control group (*secondary outcomes*).Additionally, exploratory analyses will be conducted to investigate the following:characteristics of study responders and intervention completers versus nonresponders and noncompleters;predictors of intervention effects;potential differences in intervention effects between the CBI and MBI groups;long-term consequences of the interventions related to work participation; andlong-term effects of the interventions on comorbidities, relapse or new cancers, and mortality.

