### Randomization

Once an eligible participant has submitted the CABC survey at baseline (that also implies consent to participate), the participant is allocated to 1 of the intervention groups or the control group in the ratio 1:1:1 (Figure 1). The randomization algorithm uses a variant of block randomization, with no stratification, where block sizes vary between 12, 18, 21, and 27. The output of the randomization algorithm for each participant is a string representing an access code to 1 of the 2 interventions (each intervention has a unique access code), or a string indicating that the participant was randomized to the control group. The access code is used to download the StressProffen program (an app). The randomization is performed in R studio version 1.2.1335 (The R Foundation for Statistical Computing).

Intervention identification is not possible from the access code, and participants in the 2 intervention groups are not informed to which of the intervention they have been assigned to. However, an informed participant may detect which group they are in by identifying content when using the assigned app. Hence the trial is single blinded.

After randomization, participants randomized to 1 of the intervention groups receive a letter containing information about the scheduled time for the first phone call. For participants randomized to the control group, the letter contains information about the timing of further follow-up surveys.

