### Statistical Analysis

Between-group differences in primary and secondary outcomes will be analyzed using intention-to-treat and per-protocol analyses. Continuous outcomes will be analyzed using standard *t* tests (2-tailed and unpaired) and multivariable linear and mixed regression models to adjust for potential differences between groups occurring by chance. Categorical outcomes will be analyzed with chi-square tests and multivariate logistic regression analyses. When analyzing longitudinal data, multivariate regressions with clustered standard errors, multilevel models, or generalized estimating equations may be used to account for the correlation between repeated measurements.

Potential interaction effects between the interventions and relevant covariates such as age at diagnosis, disease characteristics (triple negative, HER2+, or DCIS), and primary treatment will also be explored, either by stratification or by estimating multivariate models including interaction effects.

Missing data will be handled using multiple imputation techniques, primarily if the proportion of participants with missing information exceeds 15%. A detailed description of statistical analysis will be developed. All statistical analyses will be performed using STATA statistical software version 15 or later (StataCorp LLC).

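### The fixed 2.5% per comparison is valid, but Holm's procedure would add power for the joint primary hypothesis at no cost in participants; the per-outcome adjustment does not support the secondary hypotheses as worded

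*Protocol article*

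**What the plan says.** - **Significance level.** Sample Size Calculations describes the testing threshold as "adjusted for multiple comparisons (comparing 2 intervention groups with 1 control group for each outcome) by setting the significance level to 2.5" per cent. The stated scope is "comparing 2 intervention groups with 1 control group for each outcome". Nothing is said there about adjustment across outcomes or time points.
- **Power.** The same section plans "With an estimated 80% power to detect a difference between 1 of the intervention groups and the control group", where "the effect size was set to 3 and the SD to 6". It arrives at 235 participants needed, and 335 enrolled at 70% completion. Randomization is "in the ratio 1:1:1". Results later raises the enrolment target to 430, described as about 100 per group.
- **Primary hypothesis.** Specific Hypotheses states that CBI and MBI will each reduce perceived stress more than usual care at 6 months. This is a joint claim made of two tests.
- **Secondary hypothesis.** The same section predicts significantly larger reductions in six domains and "a significantly larger improvement in quality of life, mindfulness, sleep, coping, and work-related outcomes 13, 24, 35, and 36 months after diagnosis". Exploratory analyses are listed separately after it.
- **Analysis.** Statistical Analysis specifies t tests ("2-tailed and unpaired") and regression models, states no α level or testing order, and says a detailed analysis description will be developed.

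**The concern.** **Primary pair.** With a fixed equal split, the second comparison is still held to 2.5% after the first has been won. Holm's procedure then releases the full 5% to the second test without any added assumption. Because the primary hypothesis is that both apps work, power to show both is a relevant quantity, and it is lower than the stated 80%, which refers to one comparison.

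**Secondary outcomes.** Allowing for two arms within an outcome limits error for that outcome only. The secondary hypothesis nevertheless predicts significance, in no ranked order, on eleven domains at several times. If those results were read as confirmatory, false claims could accumulate. The article's conclusion rests its case for the apps on stress and on psychosocial and physical complaints together, so secondary results may carry weight.

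**Working it through.** **Inputs from the article:** difference 3, SD 6 (standardised 0.5), two-sided 2.5% per comparison, 80% power, 1:1:1 allocation.

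**1. The plan's own figure.** Per arm, n = 2 × (z for α/2 + z for power)² × (SD/difference)².
- Two-sided 2.5%: 2 × (2.241 + 0.842)² × 4 = 76.0, so 77 per arm and 231 in total. The exact noncentral t calculation gives 78 per arm (power 80.4%) and 234 in total. Both agree closely with 235.
- Two-sided 5%: 63 per arm and 189 in total, which does not reproduce 235.
- Enrolment: 235 / 0.70 = 336, against 335 stated.

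The split is therefore already inside the stated 80% power.

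**2. Validity of the split.** Both comparisons share the control group, so their test statistics correlate at 0.5. At 2.5% each, the chance of at least one false rejection when neither arm works is 4.65%. The split protects 5%.

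**3. Fixed 2.5% against Holm.** These are normal-theory simulations of three arms with a shared control. Under Holm the smaller p is tested at 2.5%; if it is significant, the other is tested at 5%.

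| Scenario | Quantity | Fixed 2.5% | Holm |
|---|---|---|---|
| 78 per arm, both at 0.5 SD | each arm | 81.1% | 85.5% |
| | both arms | 70.3% | 79.1% |
| | at least one arm | 91.95% | 91.95% |
| 78 per arm, only one arm effective | that arm | 81.1% | 81.2% |
| 100 per arm, both at 0.5 SD | each arm | 90% | 93% |
| | both arms | 84% | 90% |

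The 100 per arm is an assumption. It matches 430 × 0.70 / 3 = 100.3, but Results reports completion below expectation.

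**4. Secondary tests.** The article gives no count of tests. One count from Table 1, by instrument or symptom and follow-up time, leaves out the primary test and the single-item stress scale:
- perceived stress at 2 times: 2
- RAND-36, coping, mindfulness, distress, sleep, fatigue and work at 3 times each: 21
- QLQ-C30, BR23, neuropathy, vaginal symptoms and arthralgia at 2 times each: 10

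The total is 33 cells, and 33 × 2 arms = 66 tests.

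If neither app does anything, the two-sided tests split their false rejections equally between the two directions:
- False results in either direction, if independent: 66 × 0.025 = 1.65 expected; chance of at least one 1 − 0.975^66 = 81%.
- False results favouring an app, if independent: 66 × 0.0125 = 0.825 expected; chance of at least one 1 − 0.9875^66 = 56%.
- False results favouring an app, simulated with a shared control and an assumed equal correlation between cells: 37% at correlation 0.3 and 27% at 0.5.

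**The case against.** **The fixed split is not an error.** This stands. It controls the primary family, the trial is sized for it, and the stated power target concerns one arm against control. For that target, or for showing at least one effective arm, Holm adds almost nothing or nothing. A reader might infer that the plan wastes power or tests wrongly; the documents do not support that. What remains is an efficiency available for the joint hypothesis.

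**The article does not rule out Holm.** This also stands. The 2.5% appears only in the sample size section, and a Holm analysis would be sized at the same level because that is its first step. But the article names no step-down rule, so the gain is secured only if one is written down.

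**The enlarged target shrinks the gain.** True: at 100 evaluable per arm it is about 3 points per arm and 6 for both, rather than 4 and 9. It does not vanish.

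**A strategy across secondary outcomes may be left to the analysis plan.** This stands, so its absence is not a finding. The point is limited to what the article does say: a per-outcome adjustment beside unranked hypotheses of significance. A reader might also infer that secondary outcomes have no error control, or that there is an 81% chance of a false benefit. Neither holds. The two arms within an outcome are held below 5%, and 81% counts results favouring usual care as well and assumes independence. Related complaints measured repeatedly in the same women are not independent. The 66 tests are also a reviewer's count, and the longitudinal models the article allows could reduce it.

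**Conclusion.** The point holds as an inexpensive improvement, not as the correction of an error. If both apps have the planned effect, Holm raises power to show both from 70% to 79% at 78 evaluable per arm, or from 84% to 90% at an assumed 100. The gain depends on both arms working.

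The secondary part is weaker. The 2.5% level does not control error across outcomes and times, so it cannot carry the hypotheses of significant difference as written. On the count of 66 tests, the chance of at least one false benefit is about 56% at most, and roughly 27% to 37% at assumed correlations of 0.5 to 0.3. These figures indicate scale only; they are not properties stated in the plan.

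**What to change.** 1. **Primary pair.** In the detailed analysis description, state that the two primary comparisons are tested by Holm's procedure at a two-sided family-wise 5%: the smaller p against 2.5% and, if that is significant, the other against 5%.
2. **Secondary hypothesis.** Reword it so that secondary outcomes are reported as estimated differences with confidence intervals and treated as supportive, without confirmatory claims of significance.

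Both changes should be made before any comparison by arm is seen. They need wording only and no extra participants. The costs are that simultaneous confidence intervals matching Holm are less simple than those for a fixed split, and that fewer secondary results can be called significant.
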